### Method of randomization and bias minimization

Informed consent will be obtained from each participant before enrollment in the study. Patients who meet all the inclusion criteria and none of the exclusion criteria will be consecutively included and randomized into one of the four study arms (Figure 1): Individualized perioperative group; Individualized intraoperative group + postoperative CPAP; Standard intraoperative group + postoperative CPAP; Standard perioperative group.

The patients will be randomized online via the website http://iprove.incliva.es using the Mersenne Twister algorithm with an allocation rate of 1:1:1:1.

Blinding: At least two investigators are required in each participating center, because the study characteristics do not allow the blinding of investigators in the operating and postoperative room, so data acquired in these sites will not be blinded. After 24 h, all data will be acquired by the second investigator who will be blinded to the randomization arm.

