Systemic complications: Heart failure: cardiac index <2.5 ml/min/m^2^ or >2.5 when ≥5 μg/kg/min dobutamine is required. Clinical signs (hypotension, oliguria, pulmonary edema) together with NT-proBNP >13 pg/ml or echocardiographic diagnosis [34]. Systemic inflammatory response syndrome (SIRS): axillary temperature >38.5°C or <35.5°C, or central temperature of 38°C and 36°C, respectively. Heart rate (HR) >90 bpm (in the presence of atrial arrhythmia, the ventricular rate measurement will be used). If medication that could affect the HR is administered, the patient must meet the following three criteria: (a) RR >20 rpm, (b) a PaCO_2_ of <32 mmHg or use of mechanical ventilation, (c) leukocytosis of ≥12 × 10^9^/l, or leukopenia of <4 × 10^9^/l. Sepsis: infectious focus identified plus SIRS criteria. Severe sepsis: sepsis plus at least one organ dysfunction, hypoperfusion, or hypotension. Septic shock: Severe sepsis with hypotension and hypoperfusion that is unresponsive to fluids. Renal failure, following the acute kidney injury scale [35]. Anastomosis dehiscence: suture line failure with leakage of the intraluminal contents that may cause peritonitis, fistula from the wound or drain, or appearing as an abdominal fluid collection (diagnosed with imaging) that causes fever, septicemia, and shock. Abdominal abscess diagnosed with imaging techniques (CT). Surgical wound infection: following the CDC criteria [36]. Surgical reintervention required.

The secondary outcomes are the composite of postoperative pulmonary complications at 7 days and over the first 30 post-surgical days. Other secondary outcomes are: Increased ICU length of stay (LOS). Increased hospital LOS. ICU readmission in the first 30 days after surgery. Hospital readmission in the first 30 days after surgery. Mortality within 30, 180, or 365 days. The presence of plasma inflammatory markers: increased expression of interleukin 8 (IL-8), tumor necrosis factor alpha (TNF-α), and monocyte chemo-attractant protein (MCP-1). Plasma samples will be taken preoperatively and 48 h post-surgery.

The primary and secondary data outcomes will be taken 15 min and 3 h after PACU/ICU admission and at 1, 2, 7, and 30 days after surgery, with a 180- and 365-day follow-up for mortality. Plasma samples will be taken preoperatively and at 2 days after surgery. If the patient is not extubated in the operating room, the first four data time points will be taken from the time of extubation.

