### Other follow-up variables

Baseline variables will be recorded preoperatively and are age, sex, height, weight, body mass index, American Society of Anesthesiologists (ASA) physical status, sequential organ failure assessment (SOFA) score, ARISCAT [26] risk score, type of intervention, and medical history.

Intraoperative parameters recorded at three different time points (post-induction, 60 min after induction, and pre-extubation) will be: arterial blood gases, SpO_2_, FiO_2_, respiratory variables [VT, PEEP, P_aw_, P_plat_, C_rs_, respiratory system resistance (R_aw_), hemodynamics (cardiac index, PAM, and stroke volume variation (SVV) and/or pulse pressure variation (PPV)], diuresis, and temperature. Other relevant data that include the types of anesthetic drugs used, type and volume of fluids, blood loss and transfusion requirements, need of vasoactive drugs, diuresis, nasogastric tube insertion, duration of surgery, mechanical ventilation time, number of recruitment maneuvers performed, and the need for rescue therapy will also be recorded.

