### Statistical analysis

The sample size was estimated from the literature, assuming a risk of 25% for developing postoperative pulmonary or non-pulmonary complications [17], a relative reduction of 50% in the incidence of these complications with individualized alternative treatment in the groups, and taking into account the statistical power for making matched comparisons between the four groups in the study [37]; using a significance level of 5% and a power of 80% results in a total requirement of 920 patients (230 in each ventilatory management group). This figure was enlarged to 1012 (10%) to compensate for possible dropouts. The recruitment among centers will be competitive.

First, the patient baseline variables will be described and the homogeneity of these groups evaluated using appropriate statistical tests for the type of variable being analyzed (mean difference of proportions, chi-square, ANOVA, with a corresponding confidence interval of 95%). Then bivariate associations between patient characteristics, the primary endpoint, and the secondary outcomes will be performed by calculating their respective odds ratios or, in the case of a quantitative outcome, by an ANOVA test.

Following this, the association between the intervention groups and the main and secondary outcomes will be analyzed, calculating the corresponding odds ratio, or ANOVA in the case of quantitative outcomes. In all cases, respective means or proportions are estimated with their respective 95% confidence intervals. The primary outcome, pulmonary complications outcome, non-pulmonary complications, and mortality measurement analyses will be repeated using multivariate logistic regression models and adjusted to any patient characteristics that are shown to be clinically relevant by the previous bivariate analyses. Similarly, a multilevel analysis will be performed, incorporating different hospitals as random effects in order to assess whether the recruitment center influenced the results.

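### The adjusted mortality model takes its covariates from bivariate screening, which will be unstable if 30-day deaths number only about 10 to 30

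*Protocol article*

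**What the plan says.** The Study variables section of the protocol article lists "Mortality within 30, 180, or 365 days" among the secondary outcomes, and its data schedule ends "with a 180- and 365-day follow-up for mortality".

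The Statistical analysis section handles mortality in steps. Intervention groups are first compared on the main and secondary outcomes by "calculating the corresponding odds ratio, or ANOVA in the case of quantitative outcomes". For mortality, as for the primary outcome and the pulmonary and non-pulmonary complications, there is then a second step: "mortality measurement analyses will be repeated using multivariate logistic regression models and adjusted to any patient characteristics". Which characteristics qualify is settled by the data, since the model takes those "that are shown to be clinically relevant by the previous bivariate analyses". A multilevel model with hospital as a random effect follows.

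The article fixes neither the number of covariates nor the estimation method, and it gives no expected mortality. It mentions no time-to-event method.

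**The concern.** Patients are randomised to four arms "with an allocation rate of 1:1:1:1", so any model comparing all arms needs three arm terms before a covariate enters. The candidates are numerous. The Other follow-up variables section begins its list "Baseline variables will be recorded preoperatively and are age, sex, height, weight, body mass index" and runs to ten items, two of which (type of intervention and medical history) could each need several terms.

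The number of deaths, not the number of patients, limits how many terms a logistic model can carry. If 30-day deaths are few, two things go wrong:

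- Bivariate screening picks covariates largely by chance, so the adjusted odds ratios depend on which ones happened to be selected.
- If an arm has no deaths, the ordinary fit gives an odds ratio of zero or infinity for contrasts with that arm.

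At stake is whether the adjusted mortality comparison can be interpreted. A smaller matter arises at days 180 and 365: a yes/no outcome has no value for a patient last seen alive before that day, so that follow-up is used only if a further rule is added.

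**Working it through.** **The plan's own figures.** No figure is stated for mortality. The sample size reproduces: 25% against 12.5%, 80% power and two-sided 0.05/6 (six pairwise comparisons) give 230 to 235 per arm, depending on the formula, against the stated 230. Then 4 × 230 = 920, 920 × 1.10 = 1012 and 1012/4 = 253 per arm. The concern does not affect these figures.

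**Inputs.** From the article: N = 1012, four equal arms, three arm terms. Assumed: 30-day mortality m, and five covariates with one coefficient each, making 3 + 5 = 8 parameters.

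**Formulas.**

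- Expected deaths = 1012 × m.
- Deaths per parameter = 1012 × m / 8.
- Chance that at least one arm has no deaths, with equal risk in all arms = 1 − (1 − (1 − m)^253)^4. At m = 1%: 0.99^253 = 0.0787, and 1 − (1 − 0.0787)^4 = 0.279.

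**Results.**

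| 30-day mortality (assumed) | Deaths | Deaths per parameter | Chance of an arm with no deaths |
|---|---|---|---|
| 0.5% | 5.1 | 0.6 | 73% |
| 1% | 10.1 | 1.3 | 28% |
| 1.5% | 15.2 | 1.9 | 8.5% |
| 2% | 20.2 | 2.5 | 2.4% |
| 3% | 30.4 | 3.8 | 0.2% |
| 5% | 50.6 | 6.3 | below 0.1% |
| 8% | 81.0 | 10.1 | below 0.1% |

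**Sensitivity to the number of terms.** The mortality needed for ten deaths per parameter, a common benchmark, is:

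- arm terms only: 30/1012 = 3.0%
- eight parameters: 80/1012 = 7.9%
- thirteen parameters (all ten baseline items, one coefficient each): 130/1012 = 12.8%

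**Simulation.** The eight-parameter model was fitted by ordinary maximum likelihood to 400 simulated trials per rate, with no true arm effect. There was no usable fit in 27% of trials at 1% mortality, 2% at 2%, and none at 3% or 5%. Where the model could be fitted, mean covariate coefficients were only 2% to 4% above the true value. The simulation held the five covariates fixed, so it leaves out the added instability of choosing them from the data.

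**The case against.** The strongest reply is that the adjusted model is not the only mortality analysis. It repeats an unadjusted odds ratio, which has no covariates, so the shortage of deaths per parameter does not reach it. That stands, with one limit: an arm with no deaths breaks the unadjusted odds ratio too.

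It is also fair that the result depends on two inputs the article does not give. The trial enrols intermediate- and high-risk patients for major abdominal surgery. At 8% mortality the eight-parameter model would have about ten deaths per parameter. Failed fits are a material risk only near or below about 1% to 1.5%.

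A reader might infer four stronger points that the article does not support:

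- **The plan prescribes maximum likelihood.** It names only logistic regression. Maximum likelihood is the usual default, but an analysis plan not shown here could specify something else.
- **Patients lost before day 180 or 365 cannot be used.** Deaths before loss still count as events, and unknown status can be imputed. The rule for this may properly sit in the analysis plan.
- **The plan expects 10% to be lost by day 365.** "This figure was enlarged to 1012 (10%) to compensate for possible dropouts" is a sample-size allowance for a composite measured over 7 days. It does not forecast unknown vital status at one year.
- **A Cox model would cure the problem.** It has the same ratio of deaths to parameters and gives no finite log hazard ratio for an arm with no deaths. Death by a fixed day is a legitimate estimand, and replacing it is a matter of preference.

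**Conclusion.** The concern holds in limited form. The article states a rule, not merely a gap: adjusted logistic regression for mortality, with an open-ended covariate set chosen by bivariate screening. If 30-day mortality is about 1% to 3%, that rule works with roughly 10 to 30 deaths and, at eight parameters, 1.3 to 3.8 deaths per parameter. Selection on so few deaths is unstable across that range. Infinite or zero odds ratios are a serious prospect near 1% (about 28% of trials) and rare from about 2% to 3% upward.

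These sizes rest on the assumed mortality, the five assumed covariates and equal arms of 253. No event count was assumed for days 180 and 365, so the deaths-per-parameter figures apply to day 30 only. The issue touches an adjusted repeat analysis of a secondary outcome; neither the primary comparison nor the sample size is affected. It is worth correcting because the correction is cheap.

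**What to change.** For mortality only:

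1. Replace bivariate selection with a short covariate set named in advance from variables already collected, for example age and ARISCAT score. With one coefficient each this makes 3 + 2 = 5 parameters, or about 2.0, 4.0 and 6.1 deaths per parameter at 1%, 2% and 3% mortality.
2. Fit that model by Firth-penalised logistic regression, which gives a finite odds ratio even when an arm has no deaths. Intervals will still be wide, since penalisation adds no information. Keep the 30-, 180- and 365-day estimands.
3. Add Kaplan-Meier estimates by arm to day 365, with risk differences and 95% confidence intervals at the three time points. Patients lost earlier then contribute until last contact, on the assumption that loss is unrelated to the risk of death.

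The cost is small. Dates of death or last contact must be recorded at the follow-ups already planned, and the adjusted model uses fewer covariates. No extra patients or visits are needed.

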The monitoring plan is based on the modified Haybittle-Peto boundaries for stopping trials after interim analyses in the second half of the inclusion period [38,39]. Analysis of the main endpoint will be presented to the Data and Safety management board under a blinded code for allocation group. The first interim analysis will be conducted when outcome data of 460 trial participants have been obtained and/or the main endpoints for 150 participants have been documented. If this first interim analysis is significant (*P* <0.001) for benefit or harm from the intervention, a second interim analysis will be carried out when outcome data for 600 trial participants have been obtained. If this second interim analysis is also statistically significant (*P* <0.001) for benefit or harm, the Data and Safety management board will advise the Steering Committee to stop the trial.

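### A non-significant first interim look cancels the second, and the and/or trigger for the first look does not fit the planned event rates

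*Protocol article*

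**What the plan says.** All of this is in the Protocol article, Methods, Statistical analysis.

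- **Timing.** Stopping is to be considered "after interim analyses in the second half of the inclusion period", under modified Haybittle-Peto boundaries.
- **First look.** "The first interim analysis will be conducted when outcome data of 460 trial participants have been obtained and/or the main endpoints for 150 participants" are on record.
- **Second look.** If the first look has P<0.001 "for benefit or harm from the intervention, a second interim analysis will be carried out when outcome data for 600 trial participants" are in hand. If the second look also has P<0.001, for benefit or harm, the board advises the Steering Committee to stop. No other look is described.
- **Planned rates.** The sample size rests on "assuming a risk of 25% for developing postoperative pulmonary or non-pulmonary complications" and on "a relative reduction of 50% in the incidence of these complications with individualized alternative treatment in the groups". It "results in a total requirement of 920 patients (230 in each ventilatory management group"), raised by 10% to 1012.

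The Trial organization section ties the board's recommendation to continue or stop to what is collected at the interim analyses.

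**The concern.** Two features of the rule work against its purpose.

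First, the look at 600 is a confirmation step and not a second chance to detect a difference. A difference that falls short of P<0.001 at 460 and strengthens afterwards meets no further planned interim analysis. A first look that crosses for harm leads to advice under this rule only once outcome data from 140 more participants are in. Confirmation before stopping for benefit can be argued for. The plan applies the same requirement to harm and gives no reason.

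Second, the first look has two triggers joined by *and/or*, and they do not agree at the plan's own event rates. One reading places the first look at or after the second. The other makes the event clause inert, or moves the look ahead of the stated window. The board could not tell from this text when its first analysis is due.

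**Working it through.** **Inputs.** From the Statistical analysis section: control rate 25%; halving to 12.5%; two-sided 5% (sidedness assumed) and 80% power; 230 per arm; looks at 460 and 600; bound P<0.001 (|z| > 3.29). Allocation is 1:1:1:1 (Method of randomization). The harm rates of 35 to 45% below are illustrative and not in the document.

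**1. Reproducing the sample size.** The plan allows for "taking into account the statistical power for making matched comparisons between the four groups in the study". Assume this means six pairwise comparisons, so α = 0.05/6. Then n = (z₁₋α/₂ + z₀.₈₀)² × [p₁(1−p₁) + p₂(1−p₂)] / (p₁−p₂)² = (2.638 + 0.842)² × (0.1875 + 0.1094) / 0.015625 = 230.1. That gives 230 per arm, 4 × 230 = 920, and 920 × 1.10 = 1012. The 25% and 12.5% rates are therefore the ones the design uses.

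**2. Patients not covered.** 1012 − 460 = 552 (or 920 − 460 = 460 before the dropout allowance). Between the looks: 600 − 460 = 140.

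**3. What the conditional look costs.** Each look is a pooled z-test on cumulative data, z = (p̂₁ − p̂₂)/√[p̄(1−p̄)(1/n₁ + 1/n₂)]. One arm versus one arm has 115 then 150 per side; two versus two has 230 then 300. There were 1,000,000 simulated trials per row. The written rule needs both crossings. *Either* is the first column plus *only at 600*.

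| True rates | Contrast | Cross at 460 | Cross at 600 | Both (as written) | Only at 600 | Either |
|---|---|---|---|---|---|---|
| 25 v 35% | 1 v 1 | 4.9% | 7.9% | 3.7% | 4.3% | 9.1% |
| 25 v 35% | 2 v 2 | 16.9% | 26.8% | 14.7% | 12.1% | 28.9% |
| 25 v 40% | 1 v 1 | 19.1% | 30.2% | 16.9% | 13.4% | 32.5% |
| 25 v 40% | 2 v 2 | 56.0% | 74.3% | 54.4% | 19.8% | 75.8% |
| 25 v 45% | 1 v 1 | 45.7% | 64.0% | 43.8% | 20.2% | 66.0% |
| 25 v 45% | 2 v 2 | 89.3% | 97.1% | 89.1% | 8.0% | 97.4% |
| 25 v 25%, one direction | either | 0.05% | 0.05% | 0.02% | 0.03% | 0.08% |

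Hand check of the third row, unpooled: z = 0.15/√[(0.1875 + 0.24)/115] = 2.46, and Φ(2.46 − 3.29) = 0.20, close to the simulated 19.1%. Under the null, counting both directions, any crossing has probability of about 2 × 0.08% = 0.16%.

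The planned benefit, 25% versus 12.5% one against one, behaves like 25 v 40%: 16% as written and 32% under *either*.

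**4. The event trigger.** Expected events = N × pooled rate; patients needed for 150 events = 150/rate. I take the clause to mean 150 participants who have had the endpoint.

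| Arms at 25% / 12.5% | Pooled rate | Events at 460 | Patients for 150 events | Chance of 150 by 1012 |
|---|---|---|---|---|
| 1 / 3 | 15.6% | 72 | 960 | 77% |
| 2 / 2 | 18.75% | 86 | 800 | >99.9% |
| 3 / 1 | 21.9% | 101 | 686 | >99.9% |
| 4 / 0 | 25% | 115 | 600 | >99.9% |

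The chance of 150 events by 460 patients is at most 0.00015 in every row.

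- Read as *and*, the first look falls at about 600 to 960 patients, at or after the second.
- Read as *or*, the clause acts only if the pooled rate exceeds 150/460 = 32.6%. The look then comes before 460. Since 460 is exactly half of 920 and 45% of 1012, anything earlier lies outside the second half of inclusion.

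**The case against.** Several stronger readings are tempting, and the document does not support them.

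- **That the 150-endpoint trigger can never be met.** It is out of reach by 460 patients at the planned rates, but within the trial 150 events are expected at 600 to 960 patients.
- **That late harm would never be examined.** The final analysis still tests the primary outcome. What is missing is an interim examination.
- **That the board gets only one look in most trials with a real effect.** This depends on the contrast, which the plan does not name. Two arms against two at 25 v 40% cross at 460 in 56% of trials. One arm against one at 25 v 50% cross in 74%.
- **That the rule departs from the standard Haybittle-Peto boundary.** The plan calls its version modified and cites sources not shown here, so the point has to rest on how the written rule behaves.
- **That the board is forbidden to act sooner.** The text says when it will advise stopping, not that it may not do so earlier. A board charter or adverse-event rules may exist in documents not shown.
- **That the event clause should simply go.** The composite is broad (Study variables), and a pooled rate above 32.6% is possible. With two arms at 25% and two at 40%, 460 patients give 460 × 0.325 = 149.5 expected events. Read as *or*, the clause could then bring the first look forward. The fault lies in *and/or*, not in having an event trigger.

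It is also fair that requiring two crossings is conservative: it neither inflates type I error nor biases the final analysis. All of these limits stand. None explains why a non-significant first look should cancel the second, or when the first look is due.

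**Conclusion.** The concern holds in this form. Followed as written, a non-significant first look at 460 leaves no planned interim analysis for the remaining 552 of 1012 patients, for harm or benefit. At an illustrative 25 v 40%, the chance of stopping advice is about 17% instead of 32% (one arm versus one), or 54% instead of 76% (two versus two). At 25 v 45% with two against two, the gap narrows to 89% versus 97%. Separately, the *and/or* trigger is inconsistent with the planned rates under either reading.

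The sizes rest on assumed harm rates, on an interim contrast that the plan does not specify, on pooled z-tests with equal arms, and on reading the 150 as participants with the event. If it meant 150 participants with outcome data, that trigger would come long before 460 and would also conflict with the stated window. The conditional look itself needs no assumption: it is in the text.

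**What to change.** 1. Hold the 600-participant look whatever the first result, and let P<0.001 at either look support advice to stop, at minimum for harm. If confirmation is wanted for benefit, say so and keep it for benefit only.
2. Replace *and/or* with one unambiguous trigger. One option is 460 participants with day-7 outcomes, which matches the 7-day primary outcome. If the event trigger is kept, state that the look is held at whichever of the two comes first, and reconcile this with the second-half-of-inclusion wording.
3. Name the contrast to which the interim P value refers, since the rule's performance depends heavily on it.

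Items 1 and 2 are a two-sentence change, best made before the first look. The cost is one additional interim analysis that is always performed. Per contrast, the chance of any crossing under the null is about 0.15 to 0.17%, a negligible type I error cost. If all six pairwise contrasts were monitored, the total could not exceed about 6 × 0.17% = 1.0%.
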